#### Concealment mechanism {16b}

The allocation sequence will be sequentially numbered, independently if the children were assigned to the control or study group.

#### Implementation {16c}

All the children will pass the screening visit to assure that they comply with the inclusion criteria. Once the eCRF for the screening visit was filled in fully, the researcher from the clinic will use the specific option of the eCRF to generate the allocation sequence number. The children will be automatically assigned to the control or intervention group, but only the principal investigator could access this information.

### Assignment of interventions: blinding

#### Who will be blinded {17a}

The eCRF has different access depending on the role of the investigator. Only the PI and coordinator team members can access the information about the method of correction assigned to each child.

The spectacles will be fitted in opticians’ shops that do not participate in the follow-up visits, so the study is double-blinded for the investigators of the clinics and the participants.

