## Methods: participants, interventions and outcomes

### Study setting {9}

The clinical trial is being done in the following ophthalmologic clinics in Spain and Portugal: Novovision (Madrid and Murcia, Spain), Virgen de Lujan clinic (Seville, Spain), Instituto clínico quirúrgico de Oftalmología—ICQO (Bilbao, Spain), Instituto de Microcirugía Ocular—IMO (Madrid, Spain), and Clínica Privada de Oftalmologia – CPO (Lisbon, Portugal). The trial is being coordinated by Universidad Complutense de Madrid and Instituto Superior de Educação e Ciências, ISEC Lisboa. Ethical approval was obtained from the Ethics Committee CEIm Hospital Clínico San Carlos. Written informed consent was collected from the parents/guardians and participants older than 12 years old before the enrolment. Table 1 shows the schedule of the different protocol phases: enrollment, follow-up visits, data collection, and assessment that were designed following the Standardized Protocol Items: Recommendations for Interventional Trials (SPIRIT) guidelines. The study flowchart is shown in Fig. 1.

**Table 1 Tab1:** Schedule of assessments and examination items

Date/item		Screening	Spectacles dispense	Follow-up					
		Day − 30 to day 0	V0	V1	V2	V3	V4	V5	V6
			Day 0	1 week ± 1 day	3 months ± 15 days	6 months ± 30 days	12 months ± 30 days	18 months ± 30 days	24 months ± 30 days
Informed consent signed		X							
Basic information	Demographics	X							
	History	X							
Refraction	Noncycloplegic autorefraction	X				X	X	X	X
	Subjective refraction	X				X	X	X	X
	Cycloplegic autorefraction	X				X	X	X	X
Visual acuity	Uncorrected visual acuity	X				X	X	X	X
	Best-corrected visual acuity	X				X	X	X	X
	Central visual acuity		X		X	X	X	X	X
	Peripheral visual acuity		X		X				
Eye examination	Keratometry	X				X	X	X	X
	Slit lamp examination	X				X	X	X	X
	Fundus examination	X							
	Intraocular pressure measurement	X							
	Axial length	X			X	X	X	X	X
	Choroidal thickness	X				X	X	X	X
Binocular vision	Accommodative LAG	X				X	X	X	X
	Monocular estimated method (MEM) retinoscopy	X				X	X	X	X
	Phoria (distance and near)	X				X	X	X	X
Spectacle fitting	Frame position and lens condition		X						
Questionnaires	Lifestyle	X							
	Spectacle lens performance and wearability		X	X	X

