### Interventions

#### Explanation for the choice of comparators {6b}

Optical design solutions such as dual focus/multifocal contact lenses and OK lenses based on the concept of simultaneous competing defocus have scientific evidence to reduce the progression of myopia in terms of SE and AxL [11, 13, 14, 24, 25]. This evidence-based knowledge from scientific concepts was translated into the lens design of ophthalmic lenses by taking into consideration the roughing eye. Applying simultaneous competing defocus due to cylindrical annular refractive elements, the eye experiences conflicting visual signals between the fovea and the periphery [23, 26]. These elements adopt optical microstructures with alternating defocus and correction zones, correcting myopia along the visual axis and simultaneously imposing relative myopic defocus over a large part of the retina for myopia progression management. Additionally, the back surface of the lenses is further supported by freeform optimization to correct the eye’s refractive error for all viewing angles and to minimize unintended hyperopic defocus for oblique views through the lens periphery.

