#### Intervention description {11a}

Children assigned to the study group will wear ZEISS MyoCare lenses, while those assigned to the control group will wear conventional ZEISS ClearView single-vision lenses in their spectacles. Both lenses will be made of the same material (MR8) and hard as well as anti-reflection coating (ZEISS DuraVision Platinum) and will have the same surface treatments.

The following is the general overview:Subjective refraction (endpoint: best visual acuity with the most positive sphere).Objective refraction after cycloplegia (mean of 3 measurements).Ocular biometry (five measurements using IOLMaster 700 (Carl Zeiss Meditec AG, Jena, Germany)).OCT: spectral domain OCT using volume scan (and enhanced depth imaging) to visualize the choroid (ZEISS CIRRUS 5000, Carl Zeiss Meditec AG, Jena, Germany or Spectralis de Heildebergd Engineering) for 6 × 6 mm^2^ area. The choroidal thickness will be evaluated by automatic segmentation.Slit lamp examination.Intraocular pressure.Fundus check.Parameters of wear.Monocular measurement of distance and near visual acuity.Peripheral visual acuity.Distance phoria, near phoria @ 33 cm, and accommodative lag @ 33 cm.Vision quality, visual comfort, quality of life, and frequency of visual symptoms with lens wear are to be graded by the subjects themselves through questionnaires.

Table 1 describes the different measurements taken in each of the visits.

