### Sample size {14}

Based on an annual progression of − 0.50D, an estimated minimum efficacy of 50% compared to control, a power of 80%, an alpha of 5%, and a standard deviation for objective refraction of 0.70D, the size of the sample is 124.

Taking possible dropouts into account, 150 children will be included in the intervention group and 150 children in the control group.

Assignment to the different groups will be made by stratified randomization based on the age and spherical equivalent of the child. Randomization will be done automatically at the patient level by including the parameters of the initial visit in the eCRF. The researchers from the clinics will have partial access to the eCRF so that they will only be able to access the data that they have entered or must complete, not knowing the group assigned for each child.

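### The stated double-blinding of clinic examiners relies on eCRF access and fitting site, neither of which hides the lens at visits where examiner-dependent outcomes are measured

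*Protocol article*

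**What the plan says.** All references are to the Protocol article.

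- **Who will be blinded {17a}** gives two supports. The first is access control: "Only the PI and coordinator team members can access the information about the method of correction assigned to each child". The second is the fitting site: the work is done by opticians in "shops that do not participate in the follow-up visits, so the study is double-blinded for the investigators of the clinics and the participants". The word *so* ties the double-blind conclusion to the second support. Sample size {14} repeats the first, describing clinic researchers as "not knowing the group assigned for each child", and Implementation {16c} is consistent with it.
- **Explanation for the choice of comparators {6b}** describes annular refractive elements in the study lens: "These elements adopt optical microstructures with alternating defocus and correction zones".
- **Intervention description {11a}** says "those assigned to the control group will wear conventional ZEISS ClearView single-vision lenses in their spectacles". The two products share material and coating and "will have the same surface treatments". Similar appearance is not claimed.
- **Table 1 (Study setting {9})** has a row "Central visual acuity", separate from uncorrected and best-corrected acuity. It is blank at screening, starts at dispense (V0) and recurs at V2 to V6. Subjective refraction, cycloplegic autorefraction, phoria, lag and MEM retinoscopy fall at screening and V3 to V6.
- **Outcomes {12}** makes annual progression of spherical equivalent primary without naming the refraction. Phorias and accommodative delay are among the secondary outcomes.

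**The concern.** Blinding an examiner to a worn device requires that the device cannot be told apart, or that it is out of sight when the outcome is recorded. The article describes neither. Moving the fitting to an outside shop conceals who dispensed what. Restricting the eCRF conceals the code. An examiner who sees a child in the spectacles needs neither.

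Several measurements at V3 to V6 involve examiner judgement: the endpoint of subjective refraction, phoria, and MEM retinoscopy. Screening values are recorded before allocation, so a lean that follows the lens at follow-up would not cancel out of the change from baseline. It would favour whichever arm the examiner expects to do better. The double-blind label would then promise readers more than the described procedures deliver for these measures.

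**Working it through.** **1. What each safeguard hides**

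| Safeguard | Hides the allocation record | Hides the lens from the examiner |
|---|---|---|
| Role-restricted eCRF ({14}, {16c}, {17a}) | yes | no |
| Fitting in outside shops ({17a}) | yes | no |
| Same material, coating and surface treatments ({11a}) | – | not for the annular structure described in {6b} |

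**2. Where the spectacles and the outcomes meet (Table 1)**

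| Item | V0 | V2 | V3–V6 |
|---|---|---|---|
| Central acuity | X | X | X |
| Peripheral acuity | X | X | – |
| Frame and lens check | X | – | – |
| Subjective refraction, phoria, lag, MEM | – | – | X |
| Cycloplegic autorefraction | – | – | X |

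Only the central acuity row shares visits with these outcome measures. Peripheral acuity and the item "Frame position and lens condition" fall at visits without refraction and add little. The article states no test order, no separate refractionist and no covering of the spectacles.

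**3. The plan's own figure.** Inputs from Sample size {14}: control progression 0.50 D per year, 50% efficacy (difference 0.25 D), SD 0.70 D, power 80%, alpha 5%, taken as two-sided.

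n per arm = 2 × (1.960 + 0.842)² × 0.70² / 0.25² = 123.1, rounded up to 124. The stated 124 reproduces as a per-arm number and is not in dispute.

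**4. Illustration of scale.** Assumptions not in the documents: the structure is visible; subjective refraction ends in 0.25 D steps; examiners lean one step in the expected direction in a share p of children in each arm; there is no true effect. The SD of 0.70 D is stated for objective refraction and is borrowed here.

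- Shift in the 12-month difference = 2 × p × 0.25 D. For p = 0.10 it is 0.05 D (20% of 0.25 D). For p = 0.20 it is 0.10 D (40%).
- SE = 0.70 × √(2/124) = 0.0889 D. With 150 per arm, 0.70 × √(2/150) = 0.0808 D.
- Two-sided rejection = 1 − Φ(1.96 − shift/SE) + Φ(−1.96 − shift/SE).

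| Shift | 124 per arm | 150 per arm |
|---|---|---|
| 0 | 5.0% | 5.0% |
| 0.05 D | 8.7% | 9.5% |
| 0.10 D | 20.3% | 23.6% |

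For example, at 0.05 D and 124 per arm, shift/SE = 0.56 and the two tails are 0.081 + 0.006 = 0.087. If a 24-month change is divided by two, the shifts halve to 0.025 D and 0.05 D. For an instrument reading the lean should be smaller; the documents give no basis for a figure.

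**The case against.** The strongest reply is that several links are inferred and that the primary outcome is largely out of reach. Much of this stands.

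- A reader might infer that the blind rests solely on the fitting site. It does not: restricted eCRF access is stated in the same section and elsewhere. That does not answer the point, because access control does not hide a lens either.
- A reader might infer that examiners recognise the lens before they record refraction. No order of tests is given, and sequence is a detail an article may leave to the full protocol. The article also does not say that the structure can be seen, or that central acuity is tested through the study spectacles. The latter is a reasonable reading of a row that begins at dispense, no more.
- A reader might carry the 20% and 40% shifts over to the primary result. The documents point the other way. The sample size uses an SD for objective refraction, Sequence generation {16a} stratifies on objective refraction, and {11a} defines that as the mean of three readings after cycloplegia. The lean rates have no source.
- A reader might infer that nothing in the trial could expose such a bias. Axial length, from five instrument measurements, is taken at V3 to V6. A refraction effect without an axial-length effect would be a warning, though a partial one that says nothing about phoria or lag.

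The gap in the reasoning of {17a} remains. It is a conclusion the article states, not a detail it leaves out.

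**Conclusion.** The point holds in a limited form. Section {17a} asserts double-blinding of the clinic investigators, and the measures described do not secure it for subjective refraction, phoria and accommodative lag, provided the annular structure is visible to an examiner. For cycloplegic autorefraction, the likely source of the primary spherical equivalent, and for axial length, the risk is smaller. Because Outcomes {12} does not name the refraction, that protection of the primary outcome is implied, not fixed.

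The documents do not show that examiners were in fact unblinded or that the primary comparison is biased. The false-positive rates of about 9% and 20% at 124 per arm are illustrations under assumed leans in subjective refraction, not estimates for this trial. No stated figure changes. The matter deserves correction because the remedy is cheap and the label affects how the secondary outcomes will be read.

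**What to change.** 1. **Visit order, for the remaining V3 to V6 visits.** Keep the child's spectacles in an opaque case until the pages for non-cycloplegic and subjective refraction, phoria and MEM/lag are recorded and locked. Test acuity through the study spectacles after that. Do not change the correction used for any measurement. If the full protocol takes phoria or lag through the study spectacles, leave that as it is and say that this measure is not masked.
2. **Outcomes {12}.** State that the primary spherical equivalent comes from the cycloplegic autorefraction, if that is the intent.
3. **Who will be blinded {17a}.** Replace the inference from the fitting site with the measures in step 1, or qualify the double-blind claim by naming the measures to which it applies. Where visits have already taken place, this qualification is what remains possible.
4. **Optional.** Record the examiner's guess of allocation at V6 and report it.

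Cost: an opaque case, a written visit-order instruction and, if step 4 is taken, one eCRF item. The downside is a fixed visit sequence. No change at V0 is proposed, since Trial status reports that the last child was enrolled on 25 May 2023.

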#### Procedure for unblinding if needed {17b}

We do not anticipate any requirement for unblinding, but if required, the PI and coordinator team will have access to the group allocations and any unblinding will be reported.

### Data collection and management

#### Plans for assessment and collection of outcomes {18a}

Before starting the clinical trial, all researchers from each site have been trained in the protocol and data management. A CRO will be responsible for the data management and the elaboration of the eCRF where researchers can access the last version of the protocol.

Before the inclusion of the first patient, the users will be trained through the CRO training platform. In this training, the use of the eCRF application for data capturing will be explained through slides. Users will have to confirm that they understood the system and the characteristics of the studies by passing a test. Once the user has the certificate, he/she will receive the credentials to access the eCRF.

The training will be supported by the document “User Guide” which includes all the instructions for the correct use of the platform. The users can find this guide in the section “Documents” on the platform.

The investigator and the study team will also be provided with a CRO contact for any questions or problems related to the system.

Regarding the data entry, as eCRF, it will be done directly by the users. After the capture of the data, pages must be locked, thus allowing the data manager (DM) to begin the data review.

Only the principal investigator will be able to validate the data captured in the eCRF by electronically signing the eCRF pages.

The DM of the CRO will execute a biweekly validation of the data will detect the errors that were not rectified during the process of data capture and data monitoring and will issue an online query to the investigator to solve the discrepancy.

#### Plans to promote participant retention and complete follow-up {18b}

To promote participant retention:All participants have been assigned to one investigator who is in contact with the participants and their parents during the whole study, solving any problems (broken spectacles, blurred vision, etc.).In addition, annual reports will be done for parents to know the evolution of myopia.Parents are also informed that all the children belonging to the control group that completes the 2-year study will be offered a spectacle to control myopia.

#### Data management {19}

The data management team from the CRO is specialized in capture, treatment, and data communication besides the designed processes for data management. This system will be used in the patient log, data capture, validation, query management, data coding, and extraction.

All documentation related to the database build and its validation will be kept in the data management study file (DMSF).

The clinical data management system (CDMS) will be built by the CRO using the ENNOV Capture System. ENNOV Capture System complies with RGPD UE Regulations regarding IT systems used in clinical trials, electronic signature, ICH E6 (R2), and FDA requirements.

#### Confidentiality {27}

Access to the eCRF is restricted by user password and role permission access. Logins and passwords are used to protect against unauthorized access to the database. The first time that the user connects to the platform, the system will request a password change. The password must have at least 8 characters.

Each user will be assigned to a pre-defined role (for example, CRA, data manager, investigator, read-only access) based on a job function that will determine access to specific tasks.

User accounts will be created by the CRO using the CSAdmin module or CSOnline, as appropriate. The DM will activate each new user after completing online training. The DM will ensure each role is enforced within the system and will send a confirmation email with the access data to the requester.

Permissions are personal and non-transferable. Permissions will be revoked upon notification of user termination, changes in project assignments, or study completion.

All medical data passing through the Internet network between browsers and the web server are encrypted with a 128-bit SSL certificate. In the case of computer hacking, medical data cannot be unveiled.

The activation of the security certificate can be verified by clicking the padlock in the web browser URL.

After 2 min of inactivity, the last data entered is automatically saved.

Other security information to take into account:Duration of password validity (months): 30 days by default (can be changed if necessary)Account expiration date: none by default (it is possible to define an expiration date)Automatic logout after a period of inactivity: 20 min by default (it cannot be changed)Account blocking: after 5 unsuccessful attempts to login

Each entry in the electronic audit trail will contain the date and time of action, author, data entry number, old value, new value, type of action (addition, modification, or correction), and the reason for the modification. All data captured in the eCRF will be collected in the audit trail.

#### Plans for collection, laboratory evaluation and storage of biological specimens for genetic or molecular analysis in this trial/future use {33}

Na.

Biological specimens have not been used in this clinical trial.

## Statistical methods

Data transfers will be sent to the PI from the CRO in SAS format and in Excel, and all databases will be included in one table per page. The data will be transferred by email using a compressed file (.zip) protected with a password. The database will be accompanied by the annotated eCRF (eCRF with the name of each variable impressed in it) to correctly locate each variable.

A validation will be performed before the final data transfer. This validation will include the following:A structure review to ensure the veracityA manual review of five records between the database and the files to assure that the data was correctly exportedA review of the variables that appear in each tableA verification of the total records of each table

### Statistical methods for primary and secondary outcomes {20a}

The statistical analysis of this study will be made by a statistician who will participate in the entire process of study design, implementation, data management, analysis of study results, and summary. Once the study protocol and CRF are completed, the statistical analysis plan will be finalized before the study data is locked to complete the statistical analysis report.

Statistical analysis will be performed using Stata. The statistical description and inference of the data will be based on the characteristics of the data and the selection of applicable descriptive indicators and hypothesis testing methods.

Efficacy analyses will be performed based on the full analysis set and per the protocol set. All baseline demographic analyses will be performed based on the analysis set.

The data included will be analyzed using the applicable statistical methods according to their distribution characteristics. Unless otherwise specified, quantitative endpoints will be described by calculating the mean, standard deviation, median, minimum, maximum, lower quartile (Q1), and upper quartile (Q3), and the categorical assessments will be described by calculating the number and percentage of subjects. Quantitative endpoint cluster comparisons will be performed using the cluster *t*-test, or Wilcoxon rank sum test depending on the data distribution, and categorical endpoint cluster comparisons will be performed using the chi test—square or the exact probability test.

For studies of the evolution of the progression of myopia, ANOVAs of repeated measures or Kruskal–Wallis tests will be performed.

Finally, to study how the age and graduation of the child at the start of treatment are affected, a linear regression model will be built to assess the annual change in myopia and axial length analyzing data from the right eyes of all children, what is a standard practice in this kind of studies [29–32].

All statistical tests will be determined to be statistically significant based on *P* < 0.05.

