### Outcomes {12}

#### Primary outcome

The primary outcome is to compare the mean annual progression of the spherical equivalent between myopic children treated with ZEISS MyoCare lenses and those who wear a conventional single-vision lens.

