### Assignment of interventions: allocation

#### Sequence generation {16a}

The randomization has been programmed with minimization using 3 study variables for group stratification of sex, age group, and objective refraction group (spherical equivalent):Sex (2 options): male/femaleAge (2 options): 6–9 years/10–13 yearsSpherical equivalent (6 options): [− 0.5, − 1.25], [− 1.25, − 2], [− 2, − 2.75], [− 2.75, − 3.5], [− 3.5, − 4.25], [− 4.25, − 5]

The values will be computer-generated and assigned to the patients as A for the control group and B for the study lenses, with a 1:1 ratio.

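### The test for the primary outcome is unadjusted and chosen from the data, although allocation is minimised on sex, age and baseline spherical equivalent; one pre-specified adjusted model would be a free improvement

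*Protocol article*

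**What the plan says.** **Outcome.** The Primary outcome section sets out to "compare the mean annual progression of the spherical equivalent" between the two lens groups, so the target is a difference in means.

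**Allocation.** Section {16a} states: "The randomization has been programmed with minimization using 3 study variables for group stratification of sex, age group, and objective refraction group". It gives two levels for sex, two for age and six for spherical equivalent, with a 1:1 ratio. Section {14} describes allocation differently: "Assignment to the different groups will be made by stratified randomization based on the age and spherical equivalent of the child". Sex is absent there and the method has another name.

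**Test.** Section {20a} gives one rule for between-group comparison of quantitative endpoints: a t-test (called a *cluster* t-test) "or Wilcoxon rank sum test depending on the data distribution". It names no covariate. The repeated-measures ANOVA or Kruskal–Wallis tests in the same section name none either. The only model with baseline covariates is a linear regression meant to study the influence of age and baseline refraction. It omits sex and is not named as the treatment comparison. No other section gives the primary outcome a different between-arm test.

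**The concern.** Minimisation forces the arms to resemble each other on the chosen factors. If those factors predict progression, the difference between arms varies less from trial to trial than under simple randomisation. An unadjusted t-test does not know this. It still counts the variation due to age and baseline refraction as noise, so its standard error and confidence interval are too wide and it rejects a true null less than 5% of the time. The plan itself suggests that the factors matter: it balances on age and baseline refraction, makes their relation to progression a secondary objective, and models them.

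Two further problems do not depend on how prognostic the factors are. A Wilcoxon rank sum test neither tests nor estimates a difference in means, so falling back on it would leave the stated outcome unanswered. And letting the observed distribution choose the test means that the primary method is not fixed in advance.

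At stake are precision and power from data already collected, and a primary result that matches the primary outcome.

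**Working it through.** **Inputs from section {14}**
- Control progression: "Based on an annual progression of − 0.50D".
- Effect: "an estimated minimum efficacy of 50% compared to control", so the difference is 0.50 × 0.50 = 0.25 D per year.
- Spread: "a standard deviation for objective refraction of 0.70D", with no reduction for covariates.
- Power 80%, alpha 5%. Sidedness is not stated.

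**Step 1: reproduce the plan's figure.** n per arm = 2 × [SD × (z₀.₉₇₅ + z₀.₈₀) / difference]² = 2 × [0.70 × (1.960 + 0.842) / 0.25]² = 123.07, rounded up to 124. The stated 124 is therefore a per-arm figure for a two-sided test (one-sided would give 97), and it was calculated for an unadjusted comparison. Enrolling 150 per arm implies a dropout allowance of 1 − 124/150 = 17.3%.

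**Step 2: effect of adjustment.** Let R² be the share of outcome variance explained by the minimisation factors. The documents do not give it, so 0 to 0.3 is an assumed range. The residual SD is 0.70 × √(1 − R²), the standard error is that SD × √(2/n), and power = Φ(0.25 / standard error − 1.96).

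For example, at R² = 0.2 and 124 per arm the residual SD is 0.626, the standard error is 0.626 × √(2/124) = 0.0795, and 0.25/0.0795 − 1.96 = 1.18, which gives power of 88%.

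| Assumed R² | Residual SD (D) | Power, 124 per arm | Power, 150 per arm | 95% CI half-width, 124 per arm (D) | n per arm for 80% |
|---|---|---|---|---|---|
| 0 | 0.700 | 80.3% | 87.1% | 0.174 | 124 |
| 0.1 | 0.664 | 84.2% | 90.3% | 0.165 | 111 |
| 0.2 | 0.626 | 88.2% | 93.3% | 0.156 | 99 |
| 0.3 | 0.586 | 91.9% | 95.9% | 0.146 | 87 |

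The gain over the planned 80.3% at 124 per arm is 3.9, 7.9 and 11.6 percentage points.

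**Step 3: the unadjusted test under minimisation.** This was simulated with 248 children, the three protocol factors and 3,000 trials per scenario. Assumptions not in the documents are a biased coin of 0.8, uniform age and baseline refraction, normal errors, and R² split 80:20 between age and baseline refraction.

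| Assumed R² | Mean reported standard error, t-test | True SD of the estimate | Type I error, t-test | Type I error, ANCOVA | Power: t-test / Wilcoxon / ANCOVA |
|---|---|---|---|---|---|
| 0 | 0.0887 | 0.0891 | 5.3% | 5.4% | 80% / 78% / 80% |
| 0.1 | 0.0888 | 0.0855 | 4.1% | 4.8% | 82% / 80% / 85% |
| 0.2 | 0.0887 | 0.0809 | 3.4% | 5.0% | 82% / 79% / 88% |
| 0.3 | 0.0889 | 0.0776 | 2.4% | 4.7% | 83% / 81% / 91% |

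The reported standard error is too wide by about 4%, 10% and 14% at R² = 0.1, 0.2 and 0.3. Repeats under other settings (for example 300 children and a coin of 0.85) put the t-test's type I error at 3.7–4.1%, 3.0–3.4% and 1.9–3.0%. The direction is stable and the exact size is not. Minimisation itself helps the t-test slightly, so the simulated gap between t-test and ANCOVA (about 3, 6 and 8 points) is smaller than the gain over the planning figure in Step 2.

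**The case against.** The article says that a statistical analysis plan will be finalised before data lock, and covariate lists are commonly left to it. The test sentence covers quantitative endpoints in general, and nothing excludes adjustment. This stands in part: absence of a covariate list alone would be no finding. But the article is not silent. It states an unadjusted comparison and lets the data choose between two tests, and that wording is fixed badly whatever the analysis plan adds.

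It can also be said that nothing is broken, and this stands. The sample size used the unadjusted SD, so sample size and t-test agree with each other. A conservative test produces fewer false positives, not more. If the factors explain nothing, adjustment brings nothing.

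Three stronger readings are tempting and not supported:
- A reader might infer that the 5% level or the planned power fails. Neither does: the error rate can only fall below nominal in the cases examined, and the planned 80% is retained.
- A reader might take *cluster* literally and conclude that a cluster-level test is planned for individually randomised children. The same word is attached to the categorical comparisons, and section {14} places randomisation at patient level, so it evidently means *group*.
- A reader might infer from {14} and {16a} that the allocation factors cannot be known. Section {16a} is the dedicated section, lists every factor and level, and says that the scheme is already programmed. The two descriptions do conflict and need reconciling, but this is a reporting inconsistency.

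**Conclusion.** The point holds as a free improvement. The published rule for the primary comparison ignores the factors on which allocation is minimised, is not fixed before the data are seen, and allows a test that does not address a difference in means. The last two follow from the text alone.

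The cost of ignoring the factors depends on R², which the documents do not give: nil at R² = 0, and about 4 to 12 power points against the planned 80% at 124 per arm for an assumed R² of 0.1 to 0.3. The degree of conservatism also depends on the biased-coin probability, which is not stated. None of this threatens the validity of a positive result from the t-test.

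**What to change.** Before database lock and before any unblinded analysis:

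1. In {20a}, name one primary analysis: a linear model (ANCOVA) of annualised change in spherical equivalent on arm, with baseline spherical equivalent and age as continuous covariates and sex as a factor. Report the adjusted mean difference with its 95% confidence interval, and say how the change is annualised, so that the estimate matches the primary outcome.
2. Keep the t-test and the Wilcoxon test as sensitivity analyses only, and remove the data-dependent choice between them for the primary outcome.
3. Make the allocation text in {14} and {16a} agree on the method and on whether sex is a factor.
4. Replace *cluster* by *group* in {20a}, as a wording correction.

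Clinic is not a minimisation factor in {16a}, so the argument here does not call for it as a covariate. The cost is wording only: the factors named in {16a} are needed for allocation and so are already recorded at screening. Sample size and visits do not change.
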